## 5. Statistical Analysis

### 5.1. Data Management

Questionnaire data, both from the three evaluation moments and from the six educational visits, will be double entered by CISA’s data loggers into digital forms forming an Open Data Kit (ODK) aggregate server. Afterwards, these files will be converted into Excel sheets and exported to SPSS for statistical analysis. Anthropometric indices will be extracted from the Excel files produced and entered into a WHO Anthro software (version 3.2.2, WHO, Geneva, Switzerland ) to calculate z-scores and classify malnutrition. The laboratorial data will also be similarly entered into Excel® (Microsoft Corporation, Redmond, Washington, DC, USA) files and exported to IBM SPSS software, version 24 (IBM Corp, Armonk, NY, USA) for statistical analysis.

### 5.2. Baseline Assessment Eevaluations

The nutritional quality of children’s diets (24–36 months) will be determined in accordance with the Children’s Individual Dietary Diversity Score Indicator (IDDS) [69,70]. The prevalence of malnutrition in children will be calculated by WHO Anthro software (version 3.2.2). The chi-square test will be used to compare proportions, in addition to calculating the attributable fractions.

Pre-and post-intervention and intervention versus control arms evaluations.

Primary and secondary impact indicators will be evaluated between the baseline and the follow ups (for each study sample), and between the intervention and control arms. Outcomes will be compared analyzing for variance in the continuous variables and logistical regression for the categorical variables. Adequacy and plausibility arguments will be used, by analyzing the process indicators (described in Table 2) in accordance with the conceptual maps. Relative risk will be calculated in order to compare the cumulative incidence of anemia among the intervention and control arms.

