### 2.3. Participants

All under-4 children and their mothers/caretakers, resident in the selected hamlets, will be considered eligible and invited to participate. This age group was selected because children are expected to have limited mobility, to receive higher parental attention and to have their exposure to contaminated environments more controllable than school aged children. Children will be subject to exclusion whenever having recently received blood transfusions, report adverse reactions to albendazole and/or to praziquantel, and when their caretakers do not commit to completing both the evaluation and the educational moments of the study. Only children with pre-intervention evaluation will be allocated to the Randomized Controlled Trial (RCT).

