### 3.6. Recruitment and Promotion of Adherence

To relocate families, field technicians will perform a house-to-house invitation strategy, using Dande’s HDSS household identification system, reference points and family phone numbers. To increase adherence and promote participant retention, the hamlet coordinators and/or traditional authorities will be invited to be present at all phases of the study. Furthermore, incentive kits will be distributed to all children during the follow up moments, namely a nutritional kit (water and yogurt) and a WASH/Malaria kit (soap and lye).

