## 4. Data Collection

### Educational Interventions

Caretakers participating in the intervention arms will have a monitoring file (consisting of six structured questionnaires (one for each monthly visit), applied by the technician to document behavioral alterations at every counselling visit and to record attendance to the community group sessions. Those educational interventions will be intercalated with cross-sectional evaluations. Those moments will have the same design as the baseline assessment, occurring respectively six and twelve months after the beginning of the study.

Data on the primary and secondary outcomes, which will be collected only in the follow up moments, aim at evaluating the impact of interventions. Considering that interventions are expected to influence either health and behavioral aspects, impact indicators are expected to provide information on changes in their frequency, and potential associations. On the other hand, data on the process indicators, which will be collected throughout the study, aim at assisting the evaluation of the quality and success of intervention’s delivery process. Thus, data regarding the provision, utilization and coverage aspects of the delivery process are expected to facilitate attributing the changes in primary and secondary outcomes to the intervention, by demonstrating that the intervention was of sufficient magnitude and occurred in a temporal sequence. Specifically, (1) provision indicators are expected to inform about the quality of provider’s training and performance, and if the requirements for provider’s optimal performance was delivered to them; (2) utilization indicators are expected to inform about the quality of receiver’s sensibilization, their receptivity to interventional activities, acquired knowledge and alterations of inadequate behaviors toward children; and (3) coverage indicators aim at providing information regarding the quality of the interventional activities, such as the adherence to them.

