1. Primary outcomes 1.1 Impact on health - Variation of hemoglobin levels; - Anemia prevalence reduction. 2. Secondary outcomes 2.1 Impact on Health - Iron deficiency anaemia reduction; - Micronutrient deficiencies (iron, folate, vitamins A and B12, zinc and vitamin E serum levels); - Prevalence reduction, intensity, incidence and reinfections rates of STH, *P. falciparum* and *S. haematobium*; - Prevalence reduction of Stunting (height-for-age) and wasting (weight-for-height). 2.2 Impact on Behavior - Exclusive breastfeeding (0–5 months) and continued breastfeeding (12–15 months) [68]; - Increase of Minimum dietary diversity prevalence (6–23 months) [68]; - Increase of Minimum Meal Frequency prevalence [68]; - Increase of iron and vitamin A rich foods consumption; - Reduction of morbidity from diarrhea (reported).	1. Acquired knowledge - Theoretical test scores (evaluation of knowledge); - Practical test scores (evaluation of counseling performance); - Self-counseling efficacy evaluation. 2. Counseling performance - Number of families dropping outs from evaluation moments per technician; - Number of families successfully visited for counseling by each technician; - Number of notified participants present in each community groups per technician; - Number of scheduled visits held successfully per technician.	1. Acquired knowledge of receivers -Theoretical test scores; - Practical test scores (participation in community groups); - Self-evaluation at mother-to-child care. 2. Participatory level of receivers (adherence) - N° of attendances to evaluation moments; - N° of scheduled visits (both in person and by telephone call) held successfully; - N° of scheduled visits that had to be redials due to absence or unavailability; - Mood state of the receiver between visits; - N° of attendances to communitarian group. 3. Household environment evaluation (observation) - N° of household hand washing mechanisms; - N° of communitarian latrines around the house; - Cleaning conditions classification of household latrines (if existent); - Cleaning conditions classification of the backyard; - Presence of pets loose in the yard and stool. 4. Mother-to-children care practices - Children using bednets; - Children sidewalks; - Children with clean nails.	1. Services provided at evaluation moments - N° of hospital-based consultation held for parasite treatment; - N° of domiciliary-based consultation held for parasite treatment; - N° of hospital-based consultation held for sickle-cell follow up; - N° of children referred to the emergencies with severe anemia, severe malnutrition and non-malarial fever who reported to have been followed. 2.Participatory level of receivers (adherence) - Proportion of child-caretaker pair present in all evaluation moments; - Proportion of child-caretaker pair presenting in all counseling moments; - Proportion of caretakers participating in all community groups; - N° of notified child-mother pair failing the hospital-based consultations for parasite treatment or sickle-cell follow up; - N° of child-mother pair failing to picking up the sickle-cell drugs.

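### Section 5.2 assigns ANOVA and logistic regression to before-after comparisons on a followed cohort, so pre/post p-values and intervals are wrong, most clearly for anemia prevalence.

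*Protocol article*

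**What the plan says.** Section 5.2, under its line on pre- and post-intervention and between-arm evaluations, sets two kinds of comparison: "Primary and secondary impact indicators will be evaluated between the baseline and the follow ups (for each study sample), and between the intervention and control". One sentence then gives the methods for both: "Outcomes will be compared analyzing for variance in the continuous variables and logistical regression for the categorical variables". The article names no paired, repeated-measures, mixed, GEE, conditional-logistic or McNemar method.

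Three other places show that the same children are measured at each wave:
- Section 2.3: "Only children with pre-intervention evaluation will be allocated to the Randomized Controlled Trial (RCT").
- Section 3.6: "To relocate families, field technicians will perform a house-to-house invitation strategy". It uses the surveillance system's household identifiers to do so.
- Table 2, coverage indicators: "Proportion of child-caretaker pair present in all evaluation moments".

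Section 4 places the follow-up waves at 6 and 12 months with the baseline design, and also says: "Those educational interventions will be intercalated with cross-sectional evaluations". The primary outcomes in Table 2 are "Variation of hemoglobin levels" and a reduction in anemia prevalence.

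**The concern.** A child's hemoglobin or anemia status at baseline is correlated with the same child's status six or twelve months later. A before-after test on a cohort has to use that correlation. Ordinary logistic regression with wave as a covariate does not: each row counts as a different child. One-way ANOVA across waves has the same fault.

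Both primary outcomes can be affected, because the before-after comparison is planned explicitly for primary and secondary indicators. The error rates of those tests and the coverage of their intervals would not be the nominal ones. This is separate from the hamlet problem: a constant hamlet effect does not account for a child's correlation with itself.

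**Working it through.** **Inputs.** The article gives no within-child correlation, sample size or power, so there is no figure of its own to reproduce. Anemia prevalence of 57% comes from section 1. The within-child correlation rho, the number of children, the children per hamlet m and the hamlet-by-wave share of variance tau are assumptions, shown over a range.

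**Step 1: ignoring the child, with no hamlet variation.** For n children measured twice with standard deviation s:
- True variance of the mean change: 2 s² (1 − rho)/n.
- Variance used by an independent-sample test: 2 s²/n.
- Ratio of standard errors: 1/√(1 − rho).
- True size of a nominal two-sided 5% test: 2[1 − Φ(1.96/√(1 − rho))].
- Power where the paired test has 80%: Φ(1.96 + 0.84 − 1.96/√(1 − rho)).

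| rho (assumed) | SE ratio | True size | Power (paired = 80%) |
|---|---|---|---|
| 0.2 | 1.12 | 2.8% | 73% |
| 0.3 | 1.20 | 1.9% | 68% |
| 0.5 | 1.41 | 0.6% | 51% |
| 0.7 | 1.83 | 0.03% | 22% |

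A simulation under no change (4,000 runs, 300 children assumed, prevalence 57% for the binary case) agrees. At rho 0.5 the size was 0.6% for one-way ANOVA and 0.6% for logistic regression. It was 5.3% for the paired t-test and 4.9% for McNemar.

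**Step 2: a binary example.** Take anemia falling from 57% to an assumed 47% in an assumed 200 children, with wave-to-wave correlation 0.40.
- Binomial variances: 0.57 × 0.43 = 0.2451 and 0.47 × 0.53 = 0.2491.
- Independent-sample SE: √[(0.2451 + 0.2491)/200] = 0.0497.
- True SE: √[(0.4942 − 2 × 0.40 × √(0.2451 × 0.2491))/200] = 0.0385.
- Power, unpaired: Φ[(0.10 − 1.96 × 0.0497)/0.0385] ≈ 53%.
- Power, paired: Φ(0.10/0.0385 − 1.96) ≈ 74%.

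Simulation gave 52% for ordinary logistic regression and 73% for McNemar.

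**Step 3: adding hamlet-by-wave variation.** A constant hamlet effect cancels in a before-after difference; a hamlet-by-wave effect does not. Per hamlet, in units of s², the true variance is 2[(1 − rho − tau)/m + tau], and the naive test uses 2/m. The last column is a model with a child effect but no hamlet-by-wave term, which uses 2(1 − rho)/m.

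| m | rho | tau | Naive SE / true SE | Size, naive | Size, child effect only |
|---|---|---|---|---|---|
| 50 | 0.3 | 2% | 0.77 | 0.13 | 0.21 |
| 50 | 0.5 | 2% | 0.82 | 0.11 | 0.26 |
| 100 | 0.3 | 2% | 0.61 | 0.23 | 0.32 |
| 100 | 0.5 | 2% | 0.64 | 0.21 | 0.38 |

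Example for the last row: true variance 2(0.48/100 + 0.02) = 0.0496; child-only variance 2 × 0.5/100 = 0.010; ratio √(0.010/0.0496) = 0.449; size 2[1 − Φ(1.96 × 0.449)] = 0.38.

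The two errors cancel when tau = rho/(m − 1). At rho 0.5 that is about 1.0% for m = 50 and 0.5% for m = 100. Below that share the naive test is conservative, and above it the test is anticonservative.

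**The case against.** The strongest case against is that one condensed sentence in an article is being read too literally. Much of it limits the point:

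- **Continuous outcomes.** Analysis of variance can mean repeated-measures ANOVA, or ANOVA of each child's change in hemoglobin across arms. The second has one record per child and already uses the pairing. The article does not rule either out, so for hemoglobin the fault is conditional.
- **Between-arm comparisons.** At a single wave each child has one record and pairing is not an issue. A reader might infer that every efficacy test is invalid for this reason; the text does not support that.
- **Combining the follow-ups.** A reader might worry that the 6- and 12-month records are stacked so that each child counts twice. Nothing in the article says they are.
- **Direction.** A reader might conclude that real changes will be missed. That follows only if hamlet-by-wave variation is negligible.
- **Scope.** Some indicators cannot be paired. A child aged 0–5 or 12–15 months at one wave has left that band six months later.
- **Cross-sectional wording.** Section 4 describes the waves that way. Entry only with a baseline record, tracing of families and tracking of pairs across all waves still establish a cohort.

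What the objection does not remove is the binary case. Section 5.2 makes a positive choice of method for a before-after comparison. Logistic regression in its ordinary form does not handle repeated records, and no conditional or mixed form is named.

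**Conclusion.** The point stands in a limited form. Followed as written, section 5.2 gives wrong p-values and intervals for before-after comparisons of anemia prevalence and other binary outcomes measured on the same children. It does the same for continuous outcomes unless the ANOVA is run as repeated measures or on change scores.

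The child-level part alone widens the standard error by 1.20 to 1.41 for an assumed rho of 0.3 to 0.5. A test with 80% power when paired would then have 68% to 51%. With an assumed 2% hamlet-by-wave share and 50–100 children per hamlet, the naive test instead rejects a true null 11% to 23% of the time. The article gives neither quantity, so the net direction is open. The correlations, cluster sizes and variance shares are assumptions.

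**What to change.** Amend section 5.2 for outcomes measured on the same children at more than one wave:

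- Use a linear mixed model for continuous outcomes and a mixed logistic or GEE model for binary outcomes, with arm, wave and arm-by-wave as fixed effects.
- Include child and hamlet effects and a hamlet-by-wave term, or use GEE clustered on hamlet, with a small-cluster correction in either case. A child effect alone is not enough: under the assumptions above it raises the type I error of the arm-by-wave test to 0.21–0.38.
- Base the efficacy conclusion on the between-arm contrast that uses baseline. Take any within-arm before-after figure that is kept from the same model.
- Keep age-banded indicators, such as breastfeeding at 0–5 or 12–15 months, as cross-sectional between-arm comparisons with hamlet accounted for.

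This changes analysis wording only, since the identifiers needed to link waves already exist. The price is a more complex model. Section 2.1 counts 15 hamlets with health facilities and uses only those giving daily primary care, so convergence must be checked. The sponsor should also confirm that the planned software offers the small-cluster correction.

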## 6. Discussion

The efficacy of interventions to reduce anemia can comprise both educational and therapeutic dimensions [2].

Deworming plus nutrition education has been reported to reduce anemia from 82.0% to 55.4%, while increasing the consumption of leafy green vegetables from 44.7% to 60.6% [24]. Furthermore, exclusive educational interventions targeting nutrition improvement, increased the ability of mothers to identify malnutrition (from 15% to 99%), increased exclusive breastfeeding (79% versus 48% in the control group), translated into weight gain (0.86kg versus 0.77kg in the control group), increased vegetable feeding, nutrient-dense foods at lunch (11% difference between the intervention and control groups), dietary requirements for energy, iron and zinc, complementary feeding, and significantly reduced rates of stunting [17,18,19,20,21,35,71].

Exclusive WASH educational interventions, health education on soil-transmitted helminths and schistosomiasis, significantly increased knowledge, reduced both the prevalence of *Ascaris lumbricoides* and *Schistosoma mansoni* and the incidence of hookworms and the intensity of trichuriasis, ascaridiasis and hookworms [25,26]. When deworming is added to WASH education, the prevalence and intensity of STH decrease and school children scored higher than the control on STH knowledge [26,31]. Studies evaluating educational approaches to prevent malaria report improved knowledge regarding breeding sites, bednet use and indoor spraying, increased windows and door net usage and alongside maintaining clean environment practices and leading to a reduced number of reported malaria episodes and the incidence of fever [27,28,39,72].

There are reports of intensity reduction (for *Schistosoma haematobium, Ascaris lumbricoides*, *Trichuris trichiura* and hookworm) and variable cure rates when participants are exposed only to deworming with PZQ or ALB. However, re-infections can occur rapidly [73,74,75,76,77,78,79,80,81,82]. While some authors report that the link between exclusive drug therapy and hemoglobin increase remains inconclusive, others report that exclusively deworming (with ALB and PZQ) may increase mean hemoglobin [83,84]. Additionally, treating malaria has an important impact on anemia reduction [85].

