## Figures and Tables

**Table 1 ijerph-16-00466-t001:** Summary of the treatment given in each arm.

Type of Action	Nutrition Arm:	WASH Arm:	Control Arm
Diagnosis and treatment of: - Malaria (artemether-Lumefantrine 20/120), - Schistosomiasis (Praziquantel) - Intestinal parasites (Albendazol and Tinidazol) Implemented at the baseline and then every 6 months until the end of the study.	Provided	Provided	Provided
Distribution of bednets at the baseline	Provided	Provided	Provided
Distribution of soap and lye at the first and second follow ups	Provided	Provided	Provided
Personalized, home-based counseling of primary caretakers	Provided	Provided	Not provided
Targets within the educational package Each visit will address 2 behaviors of the specified targets topics, moving to the next pair in later visits	(1) Breastfeeding; (2) Complementary feeding *; (3) Weekly adequate food diversity; (4) Appropriate number of meals; (5) Adequate amount of food; (6) Responsible feeding; (7) Disease and alimentation; (8) Hygiene and food safety.	(1) Bednet usage; (2) Reducing mosquito breeding sites (3) Prevention of open sky defecation; (4) Latrine cleaning; (5) Adequate hand washing; (6) Healthy backyard environment; (7) Adequate: water availability, treatment, transportation and storage; (8) Adequate personal hygiene.	Not applicable
Number of counselling visits	6	6	Not applicable
Activities within the community groups	(1) Discussion of nutritional value of foods, the effect of processing and the most common foodborne parasites; (2) Demonstration of fish-and-meat dishes; (3) Demonstration of combinations for breakfast and lunch; (4) Taste and score of recipes; (5) Distribution of illustrative notebook with recipes.	(1) Identification of focus of Soil-transmitted helminth (STH) contamination; (2) Identification of children’s risk behavior in the community; (3) Identification of household indoor resting mosquitos and outdoor breeding sites; (4) Construction of household washing hand mechanisms; (5) Correct montage of bednet; (6) Children hand-washing classes.	Not provided
Number of community group sessions	6	6	Not applicable
Total duration of the follow up	12 months	12 months	12 months

**Table 2 ijerph-16-00466-t002:** Indicators of impact, provision, utilization and coverage being collected in this study.

Impact Evaluation	Process Evaluation		
	Provision * Indicators	Utilization Indicators	Coverage * Indicators

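### Section 5.2 lists before-after change within each arm beside the arm comparison without saying which decides efficacy, and names no baseline term for the arm comparison

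*Protocol article*

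**What the plan says.** Section 5.2 sets out two evaluations in one sentence. The first is "Primary and secondary impact indicators will be evaluated between the baseline and the follow ups (for each study sample"; the second, after the bracket closes, is "and between the intervention and control arms". It then names the methods: "Outcomes will be compared analyzing for variance in the continuous variables and logistical regression for the categorical variables". A further sentence adds a between-arm measure: "Relative risk will be calculated in order to compare the cumulative incidence of anemia among the intervention and control arms". No sentence says which evaluation carries the efficacy conclusion, and no baseline value is named as a model term.

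Table 2 gives two primary outcomes, both worded as change: "Variation of hemoglobin levels" and a reduction in anaemia prevalence. Section 4 describes their timing differently: "Data on the primary and secondary outcomes, which will be collected only in the follow up moments".

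Table 1 marks as provided in all three arms the diagnosis and treatment of infections at baseline and every 6 months, "Distribution of bednets at the baseline", and soap and lye at both follow-ups. Section 3.6 gives incentive kits to all children. Section 6 states that "treating malaria has an important impact on anemia reduction".

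**The concern.** The questions in Section 1.2 are comparative: does education added to test-and-treat reduce anaemia more than treatment alone, and which education does so more? A before-after change within one arm does not address them. The shared treatment, the bednets, the kits and a year of growth all act in that arm too, and the article itself expects malaria treatment to reduce anaemia. If within-arm change may be read as evidence of impact, an arm whose education does nothing could be reported as a success.

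The between-arm comparison matters more for this reason, and it is under-specified on a point that costs nothing. Section 2.3 allows only children with a pre-intervention evaluation into the trial, and Sections 2.6 and 2.7 cover the blood collection and haemoglobin measurement, so each child has a baseline value. Section 2.1 counts 15 hamlets with health facilities, of which only those with daily primary care enter. Three arms therefore share few hamlets, and chance baseline differences between arms are a practical risk.

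**Working it through.** The article states no sample size, standard deviation, correlation or intracluster correlation, so there is no planned figure to reproduce. What follows is illustration on stated assumptions.

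**1. Shared change in anaemia prevalence, no education effect.** Inputs from Section 1: 57% prevalence in under-5 children in earlier regional work, with 16% of cases associated with *P. falciparum* and 10% with *S. haematobium*. Assumption: 200 children per arm. Formula: z = (p0 − p1) / sqrt[p0(1 − p0)/n + p1(1 − p1)/n]. It treats the two waves as independent samples and ignores hamlets.

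- All malaria-linked cases removed: p1 = 0.57 × (1 − 0.16) = 0.479. Difference 0.091, SE = sqrt(0.2451/200 + 0.2496/200) = 0.0497, z ≈ 1.8 (p about 0.07).
- Malaria- and schistosomiasis-linked cases all removed, with no overlap and no reinfection: p1 = 0.57 × (1 − 0.26) = 0.422. Difference 0.148, SE = sqrt(0.2451/200 + 0.2439/200) = 0.0494, z ≈ 3.0 (p about 0.003).
- Half of both removed: p1 = 0.57 × (1 − 0.13) = 0.496. Difference 0.074, SE = 0.0498, z ≈ 1.5.

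**2. Shared change in haemoglobin, no education effect.** Assumptions: SD 1.3 g/dL, baseline to follow-up correlation 0.5, independent children. The SD of a change is 1.3 × sqrt(2 × (1 − 0.5)) = 1.3. The chance that one education arm shows a significant rise is Φ(d / (1.3/√n) − 1.96).

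| Shared rise d (g/dL) | n = 100 per arm | n = 200 per arm |
|---|---|---|
| 0.2 | 0.34 | 0.59 |
| 0.3 | 0.64 | 0.90 |
| 0.5 | 0.97 | 1.00 |

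**3. Comparing verdicts between arms.** If each of three independent within-arm tests has power p and education has no effect, the chance that at least one education arm is significant while control is not is (1 − p)(1 − (1 − p)²).

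- p = 0.2: 0.8 × 0.36 = 0.29
- p = 0.5: 0.5 × 0.75 = 0.38
- p = 0.8: 0.2 × 0.96 = 0.19

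Setting a significant arm against a non-significant control is therefore no substitute for testing the contrast.

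**4. Gain from baseline adjustment.** For a correlation r, the individual-level variance relative to a follow-up-only analysis is 2(1 − r) for a change score and 1 − r² with baseline adjustment. The ratio of adjusted to change score is (1 + r)/2.

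| Assumed r | Change score | Adjusted | Adjusted / change score |
|---|---|---|---|
| 0.3 | 1.40 | 0.91 | 0.65 |
| 0.5 | 1.00 | 0.75 | 0.75 |
| 0.7 | 0.60 | 0.51 | 0.85 |

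**5. Adjustment alone is not enough.** Section 3.2 randomises hamlets. An individual-level test that ignores this has a design effect of 1 + (m − 1) × ICC and a type I error of 2[1 − Φ(1.96/√DEFF)]. With assumed ICC 0.01 and 50 children per hamlet, DEFF = 1.49 and the error is about 0.11. With ICC 0.05 and 100 children, DEFF = 5.95 and it is about 0.42.

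**6. Timing of the outcomes.** Section 4 restricts primary and secondary outcome data to the follow-ups. Section 5.2 compares the same indicators with baseline, and Section 4 itself says the follow-ups share the design of the baseline assessment. These statements do not agree.

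**The case against.** The sentence in Section 5.2 does plan the randomised comparison, a between-arm relative risk follows, and Section 1.2 frames every question as a comparison. A reader might infer that impact is to be judged by before-after change alone. The text does not support that, and it nowhere says that efficacy may be claimed from within-arm change. Within-arm change also has a use: Section 7 lists the effect of treatment alone among the aims and there is no untreated arm, so the control arm's change is the only information on it. All of this stands. What remains is that two evaluations are listed and neither is given priority.

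A reader might also infer that the between-arm test is definitely unadjusted and ignores baseline. That goes too far. The article names families of methods and excludes no covariates, and a condensed article may leave the list to the full plan. The haemoglobin outcome is worded as a variation, so the analysis may already be of change scores. An unadjusted contrast that respects clustering is valid under randomisation. The case for adjustment is therefore precision and protection against chance imbalance.

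The size of the shared change can be overstated too. The z of 3.0 is an upper-end case: Section 6 reports variable cure rates and rapid reinfection, and the 200 children are assumed. Nor can the planned tests be counted up into an overall false-positive rate. They are strongly dependent, since anaemia is defined from the same haemoglobin, waves share children and contrasts share arms. In the within-arm tests no change is not the expected state.

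The restriction in Section 4 is probably loose wording, meant to contrast outcomes with process indicators collected throughout. It still needs correcting.

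**Conclusion.** The point holds in a limited form. Section 5.2 leaves open whether within-arm change or the between-arm contrast decides efficacy. Within-arm change cannot isolate education, because treatment, bednets, soap and lye, kits and ageing are common to all arms. How large the shared change will be cannot be known from the article. The prevalence illustrations run from z of about 1.5 to 3.0 with no education effect, all at an assumed 200 children per arm and without allowance for pairing or clustering.

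For the between-arm analysis, the absence of a named baseline term is a missed gain and does not make the analysis invalid. At assumed correlations of 0.3 to 0.7, adjustment leaves 91% to 51% of the individual-level variance of a follow-up-only analysis and 65% to 85% of that of a change-score analysis. These ratios do not carry over directly to the hamlet level.

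Section 4 and Section 5.2 conflict on whether outcomes are measured at baseline. A reader might infer that the 6-month wave falls at half the educational dose. The article does not say how many visits precede it, so naming 12 months as the main time point is a reasonable option and corrects no error.

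**What to change.** - In Section 5.2, state that efficacy rests on the between-arm contrasts. Estimate them with adjustment for the child's baseline haemoglobin and age (baseline anaemia status and age for the binary outcome), in an analysis that respects randomisation by hamlet.
- Report within-arm changes as descriptive. Include the control arm's change for the treatment-alone aim in Section 7, noting that it cannot be separated from the bednets, kits and ageing.
- Correct Section 4 to say that primary outcomes are measured at baseline, 6 months and 12 months.
- Optionally, name 12 months as the main time point.

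The cost is wording only, settled before outcome data are analysed. The baseline values are already collected, and no visit, sample or child is added.
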